## Abstract

**Background:**

Although the overall number of cervical cancer cases is declining worldwide, the incidence of this type of cancer is increasing in regions with low human papillomavirus (HPV) vaccination and cancer screening rates. In such regions, screening pregnant women can help improve the overall screening rate. Worldwide, cervical cancer screening is shifting from cervical cytology to HPV testing, which reduces the incidence of cervical cancer and, when negative, allows for longer screening intervals. Although HPV-based screening has been shown to be at least as effective as cytology screening for lesion detection in the general population, its performance during pregnancy remains poorly characterized due to the exclusion of pregnant women in previous clinical trials.

**Objective:**

The aim of this trial is to evaluate the effectiveness of an HPV testing protocol compared with that of a cervical cytology protocol for cervical cancer screening in pregnant women.

**Methods:**

This study is a multicenter, nonrandomized, single-arm comparative trial. In total, 5000 pregnant women aged 30 years and older in their first trimester will undergo both cervical cytology and HPV testing, with follow-up at 1 year. The primary end point is to assess the noninferiority of the HPV testing protocol compared with the cytology protocol for detecting cervical intraepithelial neoplasia grade 2 or higher, adenocarcinoma in situ, and invasive cervical cancer (CIN2+) in early pregnancy. In the cytology protocol, CIN2+ cases will be defined as those detected in cytology-positive participants. In the HPV protocol, CIN2+ cases will be defined as those detected in HPV-positive and cytology-positive participants. The primary end point analysis will use a one-sided 10% noninferiority test using the method by Tango, and with 5000 cases, the study can achieve a statistical power of at least 80%. Secondary end points will include an evaluation of the persistence of negative results post partum to determine the optimal screening interval in this population.

**Results:**

The trial was funded in April 2024 and has already started. Data collection commenced in September 2024 and is scheduled to be completed by December 2026. As of March 2026, a total of 1906 participants have been recruited. Data analysis is currently planned to begin in December 2027, and the study findings are expected to be published in 2028.

**Conclusions:**

The results of this trial will clarify whether the HPV testing protocol should be adopted as the primary cervical cancer screening method for pregnant women or whether cervical cytology should remain the standard of care.

**International Registered Report Identifier (IRRID):**

DERR1-10.2196/86397

## Introduction

More than 90% of cervical cancer cases are related to human papillomavirus (HPV), with carcinogenesis initiated via persistent infection with HPV [1]. The World Health Organization advocates for a cervical cancer elimination strategy with 3 key targets: a 90% HPV vaccination rate, a 70% cervical cancer screening rate, and a 90% treatment rate for precancerous and cancerous lesions [2].

Although the incidence of cervical cancer and mortality has been declining in countries that have consistently met these targets, their global incidence continues to increase, and considerable regional disparities remain [3]. In Japan, cervical cancer cases are on the rise [4], with approximately 11,000 new diagnoses and 2900 deaths annually. Cervical cytology–based screening is a well-established method that reduces mortality [5]. However, Japan’s screening uptake rate was only 43.6% in 2022 [6]. Prenatal visits provide a valuable opportunity for screening because more than 80% of pregnant women in Japan receive cervical cancer screening during these visits [7]. In some Southeast Asian countries, including India and Indonesia, the incidence of cervical cancer remains high while screening uptake is below 50% [8,9]. In such settings, incorporating screening into pregnancy care may improve participation.

HPV testing has also been shown to reduce the incidence of cervical cancer [10]. Compared with a negative cytology report, a negative HPV test is associated with a lower risk of developing precancerous lesions and permits extended screening intervals [11]. Accordingly, global cervical cancer screening strategies are gradually shifting from conventional cytology screening to HPV screening [10], and long-term effectiveness has also been demonstrated in real-world clinical practice [12]. In Japan, an HPV testing protocol has been available since 2024 at the discretion of individual municipalities. In the HPV testing protocol (Figure 1), HPV-positive participants undergo cervical cytology; those with atypical squamous cells of undetermined significance (ASC-US) or worse receive immediate colposcopy with or without biopsy, whereas those who are negative for an intraepithelial lesion or malignancy (NILM) undergo repeat HPV testing at 1 year. In the cytology protocol (Figure 1), participants with ASC-US undergo HPV testing; those with ASC-US and who are HPV positive or with low-grade squamous intraepithelial lesion (LSIL) or worse receive immediate colposcopy and biopsy, whereas those with ASC-US and who are HPV negative undergo repeat cytology at 1 year. Under Japan’s current HPV testing protocol (Figure 1), the screening interval for HPV-negative individuals can be extended from 2 to 5 years compared with the interval under the conventional cytology protocol [13].

**Figure 1 figure1:**
[figure not shown]
Current cervical cancer screening protocol in Japan. In the human papillomavirus (HPV) testing protocol, HPV-negative cases are scheduled for another HPV test in 5 years. HPV-positive cases undergo cervical cytology. For cases positive for HPV and atypical squamous cells of undetermined significance (ASC-US), colposcopy with or without cervical biopsy is performed immediately. Repeat HPV testing is scheduled within 1 year for HPV-positive and negative for an intraepithelial lesion or malignancy (NILM) cases. In the cervical cytology protocol, cases that are NILM are scheduled for another cervical cytology 2 years later. Cases with ASC-US undergo HPV testing, and cervical cytology is scheduled 1 year later for cases with ASC-US and who are HPV negative. For cases with ASC-US and who are HPV positive or for low-grade squamous intraepithelial lesion (LSIL) or worse cases, colposcopy and cervical biopsy are performed immediately.

Pregnant women have been excluded from most HPV screening trials. Therefore, the efficacy of HPV screening in this population has yet to be determined. The aim of this trial is to evaluate the effectiveness of the HPV testing protocol compared with that of the cervical cytology protocol for cervical cancer screening in pregnant women.

A noninferiority trial design was selected for this study. The number of cervical intraepithelial neoplasia (CIN) grades 2 and 3, adenocarcinoma in situ (AIS), and invasive cervical cancer (hereafter abbreviated as CIN2+) cases detected during pregnancy is expected to be higher under the cytology protocol than under the HPV testing protocol as the cytology protocol includes a broader population for confirmatory colposcopic evaluation, making a superiority trial design for HPV screening infeasible. Large-scale studies in nonpregnant women have demonstrated that HPV testing is comparable or superior to cytology in detecting CIN and invasive cervical cancer. In addition, HPV testing allows for the extension of the screening interval when negative; therefore, even if lesion detection rates are similar, the HPV testing protocol offers meaningful clinical advantages.

## Methods

### Study Aim and Design

This is a multicenter, nonrandomized, comparative trial designed to demonstrate the noninferiority of an HPV testing protocol compared with a cervical cytology protocol for detecting CIN2+ cases in pregnant women. In this study, all participants will undergo both HPV testing and cervical cytology using cervical swab specimens collected during early pregnancy (Figure 2). Confirmatory evaluation and follow-up will be performed to satisfy each protocol, and the expected number of CIN2+ cases detected under each protocol (Figure 1) will be estimated and compared.

**Figure 2 figure2:**
[figure not shown]
Follow-up protocol of the HOPER (Human Papillomavirus Testing for Pregnant Woman: Pregnant Women Health Initiative) trial. Low-grade squamous intraepithelial lesion (LSIL) or worse cases include participants with LSIL, atypical squamous cells cannot exclude a high-grade squamous intraepithelial lesion (HSIL; ASC-H), HSIL, squamous cell carcinoma (SCC), atypical glandular cells (AGC), adenocarcinoma in situ (AIS), adenocarcinoma, or other malignancies. Atypical squamous cells of undetermined significance (ASC-US) or worse cases include participants with ASC-US, LSIL, ASC-H, HSIL, AGC, SCC, AIS, ADCA, or other malignancies. The solid lines indicate procedures performed at all participating sites, whereas the dotted lines indicate procedures performed at selected sites only. *Self-collection human papillomavirus (HPV) testing will be conducted at 2 predefined facilities. **During pregnancy, cervical cytology and/or colposcopy with or without cervical biopsy is performed every 3 to 6 months for this subset of participants. NILM: negative for an intraepithelial lesion or malignancy.

Ethical and efficiency considerations informed the decision to use a nonrandomized trial design.

### Eligibility Criteria

This study includes only pregnant women aged 30 years or older, consistent with HPV testing protocols in Japan and many other countries given that HPV screening in women in their 20s may increase false-positive results [13]. Women at less than 17 weeks of gestation are eligible because cervical cancer screening is recommended in early pregnancy in Japan [14]. The exclusion criteria were as follows: women with no cervix, women who had been previously diagnosed with cervical cancer, women who were monitored by a health care provider for a diagnosis or suspicion of CIN, and other conditions considered unsuitable for inclusion by the physician.

### Primary End Point

The primary end point is the number of CIN2+ cases diagnosed immediately following cervical cancer screening in early pregnancy.

The difference in detecting CIN2+ cases between HPV testing and cervical cytology protocols is expected to be minimal [15]. Therefore, this trial was designed to establish noninferiority of the HPV testing protocol in detecting true positive cases of CIN2+ immediately after screening.

### Secondary End Points

The secondary end points are as follows:

Comparison of the HPV testing protocol with the cervical cytology protocol for detection of CIN grades 1, 2, and 3; AIS; and invasive cervical cancer during early pregnancy and 1 year laterHPV subtype positive rate; abnormal cervical cytology positive rate; and CIN detection rate during early pregnancy per subgroup, including age, history of past pregnancies, delivery status, marital status, HPV vaccination coverage, smoking history, and oral contraceptive useHPV subtype positive rate; abnormal cervical cytology positive rate; and CIN detection rate 1 year later per subgroup, including HPV subtype results in early pregnancy, cytology results in early pregnancy, age, pregnancy, delivery status, marital status, HPV vaccination coverage, smoking history, and oral contraceptive useCIN and cancer detection rate during pregnancy and 1 year later per subgroup, including HPV subtype, cytology finding, age, pregnancy, delivery status, marital status, HPV vaccination coverage, smoking history, and oral contraceptive useComparison of cervical cytology results between this trial (Cytopick brush [Matsunami Glass Industries, Ltd] or liquid-based cytology) and conventional screeningComparison of HPV test results between self-sampling and physician samplingSelf-sampling HPV positive rate among HPV-negative and cervical cytology–negative cases 1 year laterNumber of people eligible for colposcopy or biopsy via the HPV testing protocol and cervical cytology protocolAdverse eventsComparison of the cumulative rate of lesion progression among HPV-positive pregnant women according to immunostaining results

### Baseline Screening and Colposcopy or Biopsy During Early Pregnancy

Pregnant women will be recruited from prenatal care facilities in Japan, including those affiliated with the Yokohama Clinical Research Network.

After obtaining informed consent, cervical swab specimens will be collected at less than 17 weeks of pregnancy using the BD SurePath test with the Cytopick brush for both cervical cytology and HPV testing using the BD Onclarity assay. The results of HPV testing will be classified as high-risk HPV negative or high-risk HPV positive if they are positive for any of the evaluated genotypes (HPV16; 18; 31; 45; 51; 52; 33 and 58; 35, 39, and 68; or 56, 59, and 66).

The results of cervical cytology will be classified as follows according to the Bethesda system [16]: NILM, ASC-US, LSIL, atypical squamous cells cannot exclude a high-grade squamous intraepithelial lesion (HSIL; ASC-H), HSIL, squamous cell carcinoma (SCC), atypical glandular cells (AGC), AIS, and adenocarcinoma. LSIL or worse results include participants with LSIL, ASC-H, HSIL, SCC, AGC, AIS, adenocarcinoma, or other malignancies. ASC-US or worse results include participants with ASC-US, LSIL, ASC-H, HSIL, AGC, SCC, AIS, adenocarcinoma, or other malignancies.

Participants with an abnormal cervical cytology result, except for those with ASC-US and who are HPV negative, will undergo colposcopy and, if necessary, a cervical tissue biopsy.

CIN is classified according to the World Health Organization criteria as LSIL (CIN grade 1), HSIL (CIN grade 2), and HSIL (CIN grade 3) [17]. The primary end point, CIN2+ cases, is defined based on histological diagnosis of biopsy specimens by pathologists at each participating site using the same criteria. For participants requiring diagnostic evaluation, colposcopy is performed promptly, and the timing of this procedure is recorded in the case report form, allowing it to be clearly distinguished from the 1-year follow-up.

### Follow-Up During Pregnancy and After Birth

The study follow-up scheme is shown in Figure 2. Participants with positive cervical cytology results (excluding those with ASC-US and who are HPV negative) will undergo cervical cytology and/or colposcopy with or without a cervical biopsy every 3 to 6 months and at 1 year after the baseline screening. Participants with ASC-US and who are HPV negative and those who are NILM and HPV positive at baseline screening will undergo cytology, HPV testing, and colposcopy with or without cervical biopsy at 1 year after the baseline screening. Participants who are NILM and HPV negative at baseline screening will not undergo any scheduled follow-up. However, participants who are NILM and HPV negative at 2 predetermined facilities, accounting for approximately 10% of the participants who are NILM and HPV negative, will receive a self-collection HPV testing kit 1 year after the baseline screening to evaluate the conversion rate of HPV positivity after childbirth.

At each prenatal checkup or at delivery, the participants will be asked to schedule their next visit to minimize loss to follow-up. Data obtained during pregnancy and up to the time of delivery will be retained and analyzed even for participants who discontinue the study or are lost to follow-up.

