## Discussion

In this study, the primary end point is to assess the noninferiority of HPV testing compared with cytology for detecting CIN2+ lesions during pregnancy. Secondary end points include evaluating whether participants who test negative during pregnancy remain negative post partum, thereby informing the appropriateness of screening intervals and examining the effect of false-positive results through events identified at 1 year of follow-up.

The NILM and HPV-positive group is eligible for 1-year follow-up only under the HPV testing protocol, whereas the ASC-US and HPV-negative group is eligible for 1-year follow-up only under the cytology screening protocol. However, in either group, if participants do not attend the 1-year follow-up visit, CIN2+ cases detected at that time may be underestimated. Importantly, these groups are not recommended to undergo additional diagnostic evaluation during the remainder of the pregnancy and, therefore, do not contribute to the CIN2+ detection rate during pregnancy. In this study, we focused on ensuring that missed CIN2+ cases under the HPV testing protocol are minimized in the unique clinical setting of pregnancy; therefore, the primary end point was defined as the noninferiority of the CIN2+ detection rate during pregnancy. On the basis of existing data, the HPV testing protocol is estimated to detect an additional 0.132% (6.6 of 5000) of CIN2+ cases within 1 year. Therefore, the noninferiority margin was set at 0.132%, assuming that a small number of cases not detected during pregnancy via the HPV testing protocol could be identified at follow-up. This margin is considered clinically acceptable in light of American Society for Colposcopy and Cervical Pathology guidance that immediate confirmatory evaluation is not required for populations with a risk of CIN grade 3 or higher of less than 0.4% [24]. Compared with the cytology protocol, the HPV testing protocol is expected to increase the number of individuals requiring repeat testing at 1 year by 8% (400/5000). In contrast, 87.5% (4375/5000) of the participants may be eligible for an extended screening interval from 2 to 5 years, which is expected to reduce the overall testing burden. Thus, if CIN2+ case detection during pregnancy via the HPV testing protocol is noninferior to that of the cytology protocol, introducing the HPV testing protocol would have substantial clinical value.

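### The 1-year HPV conversion rate in swab-negative women comes from a self-collection kit, so it mixes true conversion with disagreement between collection methods, in an unknown net direction

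*Protocol article*

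**What the plan says.** **Baseline status.** In Baseline Screening and Colposcopy or Biopsy During Early Pregnancy, "cervical swab specimens will be collected at less than 17 weeks of pregnancy using the BD SurePath test with the Cytopick brush", with HPV status read by the BD Onclarity assay.

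**One-year status.** Follow-Up During Pregnancy and After Birth says: "Participants who are NILM and HPV negative at baseline screening will not undergo any scheduled follow-up". The exception is a subset at two facilities, "accounting for approximately 10% of the participants who are NILM and HPV negative", who "will receive a self-collection HPV testing kit 1 year after the baseline screening to evaluate the conversion rate of HPV positivity after childbirth".

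**Use of the result.** The Discussion describes the secondary end points as "evaluating whether participants who test negative during pregnancy remain negative post partum, thereby informing the appropriateness of screening intervals". The Abstract (Methods) goes further and presents postpartum persistence of negative results as the means of settling the optimal interval.

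**Other relevant text.** Secondary End Points names the kit result neutrally, as the self-sampling positive rate at 1 year among women negative on both baseline tests. The same section lists, separately, a comparison of self-sampling with physician sampling. It does not say when or in whom that comparison is made, whether the samples are paired, or that it feeds the conversion rate.

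**The concern.** A conversion rate is a change within a woman over time, and it needs the same yardstick at both ends. Here the yardstick changes at the second time point. Two kinds of disagreement then enter the rate:

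- A kit positive in a woman whose cervical swab would still be negative is counted as a conversion. Every woman in the subset starts as swab-negative, so such a result has nowhere else to go.
- A true new infection that the kit misses is counted as persistent negativity.

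The observed rate contains both and cannot separate them. Its confidence interval would describe sampling error only. At stake is a figure meant to inform screening intervals for a large group: the Discussion says "87.5% (4375/5000) of the participants may be eligible for an extended screening interval from 2 to 5 years". If the rate is too high, a negative test in pregnancy looks less durable than it is; if too low, more durable.

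**Working it through.** **Inputs from the article**

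- NILM and HPV-negative group: 87.5% of 5000 (Table 1). 5000 × 0.875 = 4375, which reproduces the Discussion's figure.
- Kit subset: about 10% of that group. 4375 × 0.10 = 437.5, about 437 women if every kit is returned.

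**Inputs assumed, because the article gives none**

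- True 1-year conversion *a* = 3% (about 13 women), with 2% and 5% as alternatives.
- Sensitivity of the kit relative to the swab, *Se* = 0.85 to 1.0.
- Kit positivity among women whose swab would be negative, *f* = 0 to 4%.

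**Formula.** Apparent rate = *a* × *Se* + (1 − *a*) × *f*. At *a* = 3%:

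| *Se* | *f* | Apparent rate | Bias (points) | Ratio to truth |
|---|---|---|---|---|
| 0.85 | 0% | 0.0255 + 0 = 2.55% | −0.45 | 0.85 |
| 0.90 | 0.31% | 0.0270 + 0.0030 = 3.00% | 0 | 1.00 |
| 0.90 | 1% | 0.0270 + 0.0097 = 3.67% | +0.67 | 1.22 |
| 0.90 | 2% | 0.0270 + 0.0194 = 4.64% | +1.64 | 1.55 |
| 1.00 | 2% | 0.0300 + 0.0194 = 4.94% | +1.94 | 1.65 |
| 1.00 | 4% | 0.0300 + 0.0388 = 6.88% | +3.88 | 2.29 |

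The zero-bias row solves *f* = *a*(1 − *Se*)/(1 − *a*) = 0.03 × 0.10/0.97 = 0.31%.

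**In women.** At *Se* = 0.90 and *f* = 2%, 437 × 0.0464 ≈ 20 apparent conversions, of which 437 × 0.97 × 0.02 ≈ 8.5 come from the method alone. Each percentage point of *f* adds 437 × 0.97 × 0.01 ≈ 4.

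**Other true rates, at *Se* = 1.0 and *f* = 4%.** For *a* = 2%: 0.0200 + 0.0392 = 5.92%, about 3.0 times the truth. For *a* = 5%: 0.0500 + 0.0380 = 8.80%, about 1.8 times.

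**Against sampling error.** The 95% half-width at a 3% rate is 1.96 × √(0.03 × 0.97/437.5) = 1.6 points; at 5% it is 2.0 points. A bias of 1.94 points (*f* = 2%, *Se* = 1.0) exceeds the first and roughly equals the second. If only 70% of kits came back (an assumption; about 306 women), the bias would not change for given *a*, *Se* and *f*, and the half-width at 3% would be 1.96 × √(0.03 × 0.97/306) = 1.9 points.

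**The case against.** The case on the other side has several parts.

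1. *The end point is already worded correctly.* This is true of Secondary End Points. The fault lies in the purpose stated in the follow-up section and in the reading given in the Abstract and Discussion. That narrows the point but does not remove it, because those sentences say what the trial will conclude.

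2. *The article condenses a fuller protocol, and a statistical analysis plan exists.* The absence of an adjustment method is therefore no finding by itself. What stands is that the article equates a one-time self-sample result with a change over time.

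3. *A paired baseline self-sample may exist.* The Figure 2 legend says "Self-collection human papillomavirus (HPV) testing will be conducted at 2 predefined facilities", without limiting this to 1 year in that sentence, and the figure is not shown. The text describes no such sample, but it cannot be ruled out. A reader might infer that no same-method contrast is possible for any woman; the document does not go that far.

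4. *The planned comparison of self-sampling with physician sampling already covers this.* It helps only if the two samples are taken at the same time. If it sets 1-year kits against baseline swabs, it carries the same mixture of time and method, and correcting the conversion rate with it would be circular.

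5. *The bias may be small.* At *Se* = 0.90 and *f* = 1% it is 0.67 points, well inside sampling error, and the 2.3-fold figure is a corner of the assumed range. Both remarks are fair. Nothing in the article shows which part of the range applies.

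**Conclusion.** The point holds as a matter of interpretation on a secondary end point. As described, the kit measures 1-year self-sample positivity among baseline swab-negative women; conversion or persistence cannot be read from it without assumptions about agreement between the methods. Under the assumed values the apparent rate lies between 2.6% and 6.9% for a true 3%. Excess kit positivity of about 2% at full sensitivity is enough to match or exceed sampling error. These sizes are illustrative, since the true rate, sensitivity and excess positivity are all assumed.

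A reader might infer that the plan necessarily overstates conversion, because the women were selected as negative. The documents do not support that: lower kit sensitivity works against it, and the two effects cancel at *f* of about 0.31% when *Se* is 0.90 and true conversion 3%. Nor do they support any effect on the primary end point or the sample size, which rest on baseline results and early-pregnancy histology.

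**What to change.** - In Follow-Up During Pregnancy and After Birth, the Abstract (Methods) and the Discussion, replace conversion and persistence with the quantity named in Secondary End Points: 1-year self-sample HPV positivity among women negative on the baseline cervical swab and cytology.
- Where conversion or persistence is reported, give it over a prespecified range of kit sensitivity and excess kit positivity, with sampling uncertainty carried through.
- Use agreement estimates from the self-versus-physician comparison to correct the rate (for example by a Rogan-Gladen adjustment) only if those samples are paired at the same time point. State in the text whether they are.
- Base any statement on screening intervals on that range.
- Do not use the ASC-US and HPV-negative women as a same-method comparator. About 50 are expected (1% of 5000), giving about 1.5 events at 3%. They are a different population, and the article does not say how their 1-year HPV specimen is collected.

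The cost is wording and a small analysis on data already planned, with no new visits or samples. Analysis is due to begin in December 2027, so this can be settled beforehand. The drawback is a wider, less definite conversion estimate.
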